#### Neurocognitive functioning

Neurocognitive function will be assessed using a test battery specifically designed to evaluate temporo-lateral, temporo-mesial, and frontal lobe functions, including memory, language, and executive functions. All tests have been validated for use in monitoring and outcome evaluation in temporal lobe epilepsy surgery [20, 21, 52, 53]. Cognitive functions across all domains will be quantitatively assessed preoperatively and postoperatively at Visit 7 (Day 30), Visit 8 (Day 90), and every 24 weeks until the conclusion of the trial. These assessments will focus on both group-level and individual-level changes over time.

Neurocognitive test battery consists of the VLMT (duration: 30 min including 20 min break between learning and retention) for verbal memory [28, 29], Boston Naming Test (duration: max. 5 min) for naming [30] and the EpiTrack® (duration: max. 15 min) for executive functions [31].

All chosen tests are standard for monitoring epilepsy surgery and temporal lobe surgery in particular [21]. The VLMT is a verbal learning and memory test that follows a list-learning paradigm with a 15-word list (A) to be learned over five learning trials with immediate recall, followed by learning a distractor list (B) once. This is followed by free recall of list A after distraction by learning and recalling list B and again after a delay. Finally, there is a recognition trial that requires identifying list A words from a list containing list A and B words, as well as new distractor words that are phonemically or semantically related to list A and B words. The test has proven its sensitivity to temporal lobe pathology and surgery in several studies [54–60].

The EpiTrack® is a short screening test for executive functions comprising subtests which assess psychomotor speed, mental flexibility, response inhibition, fluency, working memory, and anticipation. The EpiTrack® and its subtests are sensitive to frontal lobe functioning [61, 62] and to CNS drug effects and have been used to monitor epilepsy surgery [63, 64]. The Boston Naming test assesses naming and word finding in the language domain and is a standard procedure to monitor language functions in epilepsy surgery [65, 66].

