#### Perioperative complications

Postoperative complications will be assessed by PSIs [33] and specific CSCs as previously described [34].

PSIs introduced by the Agency of Healthcare and Quality [33] will entail pressure ulcer, iatrogenic pneumothorax, vascular catheter-related infection, transfusion reaction, retained surgical item, peri- and postoperative hemorrhage, acute postoperative respiratory failure, pulmonary embolism, deep venous thrombosis, postoperative sepsis, wound dehiscence, accidental puncture or laceration, postoperative hip fracture, postoperative physiologic and/or metabolic dearrangement. Peri- and postoperative hemorrhage will be defined as PSI in case they will require further surgical therapy.

CSCs will consist of postoperative ischemic infarction, cerebro-spinal fluid leakage, wound infection, atrophic wound healing disorder, postoperative meningitis and/or ventriculitis, emypema and postoperative permanent new or worsened neurological deficits including speech and language deficits [34]. Postoperative cerebrospinal fluid leakage will be defined as CSC if further surgical/interventional therapy (surgical wound examination, transient insertion of a lumbar drainage system and/or surgical insertion of a permanent shunt system) is required. Wound infection and postoperative meningitis will be defined as CSC, if further antibiotic-based and/or surgical therapy is needed.

PSIs and CSCs will be divided into early postoperative complications occurring within the time span of day 0 until day 30 (Visit 7) as previously described [34] and late postoperative events occurring from day 31 until day 90 (Visit 8).

The outcome will be documented as resolved, resolved with sequelae, ongoing at end of study or death.

Furthermore, iatrogenic damage of the middle cerebral artery (MCA) and/or its lenticulostriate branches, the anterior choroidal artery, and the P2 segment of the posterior cerebral artery (PCA) will be collected as intraoperative complications specifically related to temporomesial surgery.

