### Primary outcome

The statistical analysis will be conducted at the Study Center Bonn (SZB) of the University of Bonn Medical Center under the direction of [name]. [name]. The primary, confirmatory analysis will compare OS between the treatment groups using a two-sided log-rank test at a significance level of 5%. This analysis will be performed on the mITT population. The log-rank test will be stratified by age group (< 50 years or ≥ 50 years) and pre-operative KPS class (70–80% vs. 90–100%). Surviving patients and those lost to follow-up will be censored at the respective time points. OS will be summarized using Kaplan–Meier curves, with median survival estimates and corresponding 95% confidence intervals reported.

A sensitivity analysis for OS will be conducted using a Cox proportional hazards model with treatment group and MGMT promoter methylation status (hypermethylated vs. unmethylated) as independent variables. If the MGMT promoter methylation status is not available, missing data for these patients will be imputed. In another sensitivity analysis for OS, a Cox proportional hazards model with treatment group and center recruitment volume (high vs. low) will be fitted. Additionally, potential prognostic factors, including age, preoperative KPS, MGMT promoter methylation status (hypermethylated vs. unmethylated), and center recruitment volume (high vs. low), will be analyzed using a multivariate Cox proportional hazard model for OS.

If OS of ATL significantly differs from that of GTR, the patient-reported QoL domain "global health status" from the EORTC QLQ-C30 questionnaire will be analyzed as a co-primary endpoint. Changes from baseline in the experimental arm (ATL) will be compared to the standard arm (GTR) to assess non-inferiority, using a non-inferiority margin of 1.6 score points per year. This evaluation will be performed on the mITT population and using a linear mixed-effects model (QoL score as dependent variable, random patient intercept, treatment group + time as independent variables, estimating a 95% confidence interval of the interaction between time and treatment).

Overall superiority of ATL will require significantly prolonged OS alongside non-inferiority in the development of global health status over time. Due to the hierarchical testing approach, no adjustment of the type I error rate is necessary.

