### Secondary outcome variables

Secondary endpoints will be analyzed descriptively in the mITT population, if not otherwise stated. QoL will be assessed using the standardized and validated EORTC QLQ-C30 and QLQ-BN20 questionnaires. These questionnaires include health-related QoL questions scored on a nominal scale (primarily values from 1 to 4). The responses to individual questions will be recorded for analysis, and questions related to the same QoL dimension (e.g., emotional well-being) will be aggregated to generate an overall score for that dimension, following the scoring manual.

The scores for different QoL dimensions in each treatment group will be analyzed descriptively based on repeated assessments throughout the trial. Analogously to the analysis of the co-primary endpoint, linear mixed-effects models will be applied to the data to evaluate potential differences in the trends of QoL measurements over time between the treatment groups.

PFS will be summarized in the same manner as OS. Median PFS time estimates and associated 95% confidence intervals will be reported. The analysis of PFS will also be performed, similarly to the primary endpoints, within the ITT- and PP-populations as well as in the small population of patients with IDHmut diffuse high-grade glioma.

Neurocognitive function will be analyzed on both the group and the individual level. Group-level analyses will be conducted using multivariable linear mixed-effects models with post hoc tests to evaluate group differences. The side of surgery (left/right) will serve as a primary independent variable alongside the study arm.

At the individual level, both objective and subjective test data will be analyzed based on categories of impairment relative to test norms at each time point. Changes will be considered individually significant if they indicate a shift between performance categories across the three assessments (*p* < 0.1).

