### Handling of drop-outs, withdrawal, and missing data

Subjects who drop out of the trial prior to randomization will be categorized as screening failures, with the reasons for drop-out documented in a comprehensive list.

Subjects who drop out of the trial after randomization will be analyzed using all available data, except for those replaced due to a disconfirming diagnosis of glioblastoma. These subjects will be excluded from the efficacy analysis.

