The rationale underpinning the ATLAS/NOA-29 trial stems from retrospective studies suggesting that ATL may offer significantly prolonged PFS and OS in patients with temporal lobe glioblastoma compared to conventional GTR [16, 25]. Additionally, retrospective data indicate that ATL maintains perioperative safety profiles comparable to those of GTR [34], while offering the added benefit of significantly improved postoperative seizure outcomes [73]. Building on the established use of ATL in epilepsy surgery [18], where the procedure involves resection of the amygdala and the anterior part of the hippocampus [19, 36], neurocognitive outcomes are a critical consideration when translating this approach to oncological neurosurgery. In epilepsy surgery, the neurocognitive effects of ATL have been extensively studied, revealing frequent impairments in visual and verbal memory functions, with manifestations differing by the side of resection [22]. In contrast, visuospatial abilities are generally preserved [22, 23]. Despite these potential deficits, ATL has been shown to maintain a high level of overall postoperative cognitive performance in patients with temporal lobe epilepsy [20, 23]. This evidence suggests that adapting ATL to the neurooncological context may allow for sufficient preservation of postoperative neurocognitive capacities while leveraging its benefits as a supramarginal resection strategy. In contrast to patients undergoing ATL for epilepsy, where compensatory reorganization of neurocognitive functions has been reported in both non-surgically and surgically treated cohorts [74–76], such adaptation is unlikely in temporal glioblastoma due to the inherently distinct disease dynamics of epilepsy and glioblastoma. Despite this, data from glioblastoma surgery demonstrate that functional status, as measured by the KPS, remains comparable between ATL and GTR [25]. While minor neuropsychological deficits may occur following the ATL approach, neurological and cognitive functions appear to be preserved at a level that supports a good QoL and facilitates daily activities, aligning with outcomes observed for GTR.

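### The cognitive analysis has no state for a living patient who cannot be tested, so the arm comparison may be biased in either direction

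*Protocol article*

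**What the plan says.** All references are to the protocol article.

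- **Secondary outcome variables, individual level.** Results are placed in "categories of impairment relative to test norms at each time point". An individual change counts if there is a "shift between performance categories across the three assessments".
- **Secondary outcome variables, group level.** "Group-level analyses will be conducted using multivariable linear mixed-effects models with post hoc tests to evaluate group differences". Study arm and side of surgery are the main factors. Secondary endpoints are descriptive in the mITT population unless stated otherwise.
- **Neurocognitive functioning.** The battery is a verbal list-learning test (VLMT), the Boston Naming Test and EpiTrack, which includes fluency. It is given before surgery and at "Visit 7 (Day 30), Visit 8 (Day 90), and every 24 weeks until the conclusion of the trial".
- **Handling of drop-outs, withdrawal, and missing data.** "Subjects who drop out of the trial after randomization will be analyzed using all available data", apart from patients replaced because glioblastoma was not confirmed.
- **Primary outcome.** The one imputation rule concerns a covariate: "If the MGMT promoter methylation status is not available, missing data for these patients will be imputed".
- **Perioperative complications.** The cranial-surgery-related complications (CSCs) to be recorded include "postoperative permanent new or worsened neurological deficits including speech and language deficits".
- **Discussion.** It states that "neurocognitive outcomes are a critical consideration when translating this approach to oncological neurosurgery", and later sets the survival gain against the risk of neuropsychological and QoL impairment.

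**The concern.** A norm-based category needs a score, and a category shift needs scores at several visits. Dominant-side tumors are eligible, and list learning, naming and fluency all depend on usable language. A patient with marked aphasia or severe cognitive decline may therefore have no score at a visit because of the very deficit that the battery is meant to detect.

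The stated rules do not deal with this patient. The available-data rule is written for drop-outs and adds nothing for someone still in follow-up who could not be tested. In the impairment and decline rates the patient leaves the denominator. The mixed model uses the patient's other visits but assumes that the missing score is predictable from the observed ones.

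At stake is how far the cognitive results can be trusted when set against survival. If the arms differ in the share of untestable patients, the comparison among tested patients is not the comparison among survivors.

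**Working it through.** **The plan's own figures.** The article gives no figure for the cognitive endpoint, no untestable rate and no impairment rate. Its overall survival (OS) design can be reproduced, and it supplies the expected numbers alive.

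- Hazard ratio = 17/27.5 = 0.618. With exponential survival, 36 months of uniform accrual and 36 months of further follow-up, the event probability is 0.879 (GTR) and 0.735 (ATL), mean 0.807.
- Schoenfeld's formula gives 136 events, so N = 136/0.807 = 168.5. Freedman's gives 141 events, so N = 174.7. The stated 170, or 85 per arm, is reproduced.
- Alive at 3 months: 85 × 0.885 = 75.2 (GTR) and 85 × 0.927 = 78.8 (ATL). Alive at 6 months: 78.3% and 86.0%.

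**Assumed inputs.** Among living patients in an arm, q is the untestable share (0 to 20%, higher in either arm). Among tested patients, p is the impaired share (30% GTR; 30% or 40% ATL).

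**Formula.** The tested-only rate is p. With untestable patients counted as impaired, the rate is R = q + (1 − q)p. The part of the ATL minus GTR difference that the tested-only comparison hides is

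H = (R_ATL − R_GTR) − (p_ATL − p_GTR) = q_ATL(1 − p_ATL) − q_GTR(1 − p_GTR).

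Positive H means that ATL harm is understated; negative H means that it is overstated.

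| q GTR / ATL | H, p = 30% / 30% | H, p = 30% / 40% |
|---|---|---|
| 5% / 10% | +3.5 points | +2.5 points |
| 5% / 15% | +7.0 | +5.5 |
| 5% / 20% | +10.5 | +8.5 |
| 5% / 5% | 0 | −0.5 |
| 10% / 10% | 0 | −1.0 |
| 10% / 5% | −3.5 | −4.0 |
| 15% / 5% | −7.0 | −7.5 |

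Example: at 5%/15% and p = 30% in both arms, R is 0.05 + 0.95 × 0.30 = 33.5% (GTR) and 0.15 + 0.85 × 0.30 = 40.5% (ATL). The difference is 7.0 points, against 0 among tested patients.

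**In patients.** At 3 months that scenario means 0.05 × 75.2 = 3.8 untestable GTR patients and 0.15 × 78.8 = 11.8 untestable ATL patients. About 71.4 and 67.0 are tested, so the standard error of the tested-only difference is √[0.30 × 0.70 × (1/71.4 + 1/67.0)] = 7.8 points. The hidden 7.0 points is close to one standard error.

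**Group means.** Assume follow-up scores with SD 1, means −0.5 (GTR) and −1.0 (ATL), and no score below −2.0. The tested-only mean is m + d, with d = φ(−2.0 − m)/[1 − Φ(−2.0 − m)], which is 0.139 (GTR) and 0.288 (ATL). The true 0.50 SD appears as 0.712 − 0.361 = 0.35 SD.

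That is a complete-case mean, not the planned estimator. A likelihood model that also uses the baseline score (equal baseline means, correlation 0.7, common slope) has a slope of 0.577 among tested patients. This leaves 1 − 0.7 × 0.577 = 0.596 of each shift: means −0.5 + 0.596 × 0.139 = −0.417 and −1.0 + 0.596 × 0.288 = −0.828, a difference of 0.41 SD. The model recovers part of the loss, not all of it.

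**The case against.** **The article is a condensation.** It names a separate analysis plan, and coding of missed tests for a secondary endpoint commonly sits there or in the eCRF. A reader might infer that the protocol restricts the analysis to completed tests. It does not say so and names no denominator; nor does it say whether a failed attempt scores at the floor. This stands as a limit on the wording. The point rests on the classification rule that is stated, which has no state for an untested survivor.

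**Direction.** A reader might infer that cognitive harm of ATL is understated. The documents do not support that. It needs more untestable patients with ATL, and no rate is given for either arm. The Discussion cites retrospective data with comparable perioperative safety and KPS. GTR patients are assumed to die sooner and may become untestable through earlier progression, which would reverse the sign.

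**Size.** A reader might take the 0.35 SD above as the loss in the planned analysis. The planned mixed model also uses earlier scores and loses less, and a sharp cut-off for testability is itself an extreme assumption.

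**Importance.** Cognition is secondary and descriptive; the decision rests on OS and on non-inferiority of global health status. Part of the harm is recorded elsewhere: language deficits as CSCs, mRS in all randomized patients, MMSE, and the BN20 communication domain. Missed evaluations are also listed as protocol violations and discussed before analysis. This lowers the priority. It does not correct the impairment rates: CSCs are recorded only to day 90 and do not name memory or executive function, the interim mRS comparison uses a severe threshold, and BN20 is self-reported and can be missing in the same patients.

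**Conclusion.** The point holds in conditional form. As written, the individual-level rule gives no category to a surviving patient who cannot be tested, and the mixed model treats that absence as ignorable. The arm comparison may therefore be biased, with the sign set by which arm has more untestable patients. With 30% of tested patients impaired in both arms and 5 to 15 points more untestable patients in ATL, 3.5 to 10.5 points of difference are hidden. With equal shares the distortion is 0 to 1 point. With 5 to 10 points more untestable patients in GTR, ATL harm is overstated by 3.5 to 7.5 points.

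All these figures rest on assumed rates and on counting every untestable patient as impaired; none is a forecast. The primary analysis and the superiority decision are unaffected. The change is worth making because the reason for a missed test is hard to recover later, and because recording it helps whichever way the bias runs.

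**What to change.** 1. Add an eCRF field, completed prospectively, for why each cognitive test was not done: language or cognitive inability, other neurological reason, logistic reason, or refusal.
2. In Secondary outcome variables, state that each visit will be reported by arm as shares tested and not impaired, tested and impaired, untestable, dead, and otherwise missing.
3. Add a sensitivity analysis in which a surviving patient untestable because of language or cognitive state takes the lowest impairment category at that visit, counts as a decline if testable at baseline, and takes the lowest scale score in the group-level model. Leave tests missed for logistic reasons as missing. Keep other neurological reasons separate, so that motor decline is not counted as cognitive impairment.

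The cost is one data field, one paragraph and little programming. The downside is that site staff who know the arm judge the reason, so the counts by reason should be shown per arm. For the same reason, the lowest-category rule is proposed as a sensitivity analysis and not as the main rule.

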### Safety analysis

All safety evaluations, including the analysis of mRS scores at six months post-randomization, will be conducted on the safety population, comprising all patients included in the trial. AE incidence will be summarized in tabular form, both for overall incidence and individual occurrence.

### Protocol violations

Protocol violations are defined as any deviations from the procedures outlined in this protocol, including missed evaluations, incorrect timing of evaluations as well as any non-adherence to the protocol that impacts the subject’s rights, safety, or welfare.

Once a subject is enrolled, it is the investigator’s responsibility to make reasonable efforts to correct any protocol violations and to ensure the subject's continued participation in the trial, if feasible. Protocol violations alone do not constitute sufficient justification for withdrawing a subject from the trial.

Protocol violations will be reported to the project leaders during the trial via monitoring reports. A comprehensive list of all protocol violations will be prepared, and their potential impact on the evaluation of the affected subjects will be critically discussed prior to statistical analysis.

### Handling of drop-outs, withdrawal, and missing data

Subjects who drop out of the trial prior to randomization will be categorized as screening failures, with the reasons for drop-out documented in a comprehensive list.

Subjects who drop out of the trial after randomization will be analyzed using all available data, except for those replaced due to a disconfirming diagnosis of glioblastoma. These subjects will be excluded from the efficacy analysis.

### Interim safety analysis

No interim efficacy analysis is planned for this trial. The DSMB will evaluate safety data from the trial and will convene at least once per year during the recruitment phase. Additionally, to ensure that the postoperative clinical status in the experimental (ATL) arm is not substantially worse compared to the standard (GTR) arm, an interim safety analysis will be conducted six months after the randomization of the 57th patient. This ensures that one-third of the planned trial population is evaluable for safety within the first six months of the trial.

For safety determination, the mRS score for each patient will be assessed six months after randomization. The rates of patients with an mRS score of 4 or higher (dichotomized endpoint) will be compared between the treatment arms.

## Monitoring and audits

Quality control and assurance during the ATLAS/NOA-29 trial will be conducted through monitoring and audits by representatives of the Clinical Study Core Unit, Study Center Bonn (SZB).

Monitoring ensures accurate and reliable data by assessing trial progress, compliance, and documentation accuracy. The monitor will review source documents, eCRFs, and facilities, and ensure adherence to protocols and AE documentation. The frequency and scope of monitoring visits are defined in the Monitoring Plan. Source Data Verification (SDV) will confirm the accuracy of CRF entries by comparing them with source data as outlined in the Monitoring Manual.

Audits may be conducted by SZB representatives to ensure compliance with ICH-GCP and trial protocols. Investigators must provide access to relevant documents and resolve any audit findings. Audit certificates will be included in the final study report.

